### Assignment of interventions and blinding

Participant assignment into the intervention group or the control group is solely based on area of residence. Participants reside in 15 *tongs* in the intervention area and 15 *tongs* in the control area, and are divided into 3 clusters matched based on mean age and residential type (apartment vs. house).

Considering the nature of the study, limited single-blinding is applied to the intervention, as participants will not be told whether they reside in the intervention or control area, but researchers will be aware of the allocation. Upon giving informed consent, participants in the intervention group will receive an explanation of the entire HWePS intervention, while control group participants will receive an explanation of only the health information component. Assignments will not be explicitly expressed to external assessors but may be inferred throughout the course of the study. An independent data analyst blinded to the assignments will receive a cleaned dataset without any identifiable information.

### Data collection

Data collection is carried out by external assessors. The research team provides a one-day intensive education program consisting of survey procedures, safety and infection education, and an item-by-item explanation. The education session is followed by a Q&A session and three mandatory practice sessions with mock cases of older adults. All outcome data are collected using a tablet PC in which survey instruments have been embedded as a weblink and/or smartphone application. Prior to data collection, all external assessors are obliged to sign to an agreement form for confidentiality concerning information about the participants obtained during the survey.

The procedure for data collection is as follows. Upon enrollment into this intervention study, the recruiting researcher schedules each participant to meet with an external assessor who will visit the participant’s house (or any place that the participant feels comfortable) to conduct the baseline survey. Except for unavoidable circumstances (e.g., resignation of assessor, scheduling issues, etc.), the same assessor is assigned to the participant for the follow-up surveys at Week 13. The contents of the data collected at each time point are described in Table 2. Communication between the research team and the assessors is facilitated through KakaoTalk for assessment scheduling and real-time technical support.

As the intervention is being conducted during the COVID-19 pandemic, special precautions are to be taken during face-to-face interviews. All assessors are given an infection prevention protocol: 1) ensuring the use of facial masks and hand sanitizers for both assessor and participant; 2) daily personal screening for any symptoms; 3) screening at the participant’s doorstep before entry for COVID-19 symptoms, a history of foreign travel within the past 14 days, or visits to a site of mass infection; 4) taking the temperature of participants and nearby family members; 5) sterilizing any equipment used during the interview before moving to the next household. Assessors are required to submit temperature logs for themselves and all participants that they interview.

### Data analysis plan

#### Effect evaluation

Descriptive statistics will be used to analyze data concerning the participants’ demographic and baseline characteristics. Baseline differences between the intervention and control group will be analyzed using an independent sample t-test or the Mann–Whitney U-test for continuous data and the Chi-square test for categorical data. The primary analysis is an evaluation of the interventional effect of the HWePS program in the intervention area as compared to the control area. We will apply mixed effects models and generalized estimating equations adjusting for sample characteristics. In case there are significant baseline differences between groups, propensity score matching methods will be used. Subgroup analyses will be performed for sociodemographic factors (e.g., age, sex, income, etc.) and health status (e.g., frailty), and two paired t-tests will be applied for those variables collected only in the intervention group. All statistical analyses will be carried out using SAS 9.4 (Cary, NC, USA) and p-values with α ≤ 0.05 will be considered significant.

Effect analysis will be conducted based on the intention-to-treat (ITT) principle, in which all participants who participated in the HWePS study will be included regardless of intervention dose or protocol adherence. Imputation methods will be implemented to handle missing data to enable ITT analysis. Sensitivity analyses will be conducted to assess the effects of inclusion in various groups within the samples.

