The self-checkup is a decision-support service that aims to help older persons assess and be aware of their own strength, weakness, and risk factors in maintaining and promoting functional capability [3]. The self-checkup service is a smartphone application-based, multi-dimensional functional assessment tool using the interRAI Check-Up Self-Version (CUSR) and other intervention-relevant items. The CUSR is a valid and reliable self-assessment tool designed to examine the health and functional status of relatively healthy community-dwelling residents by themselves or with the assistance of family members/lay helpers [27, 36]. Upon completion of a 90-item health check-up, the CUSR generates a report including key function scales and a list of clinical assessment points for common geriatric health risks (e.g., pain, falls, inactivity, smoking/drinking, nutrition, cardiovascular disease, etc.) using triggers derived from evidence-based algorithms. The self-checkup experience is expected to motivate older persons to seek appropriate health information and services relevant to their own health risks, empower them to make a self-care plan, become interested in self-care skill-building activities, and practice a healthy lifestyle, all which are the contents of the (self-)care management component of the HWePS described below.2.Personalized care management featuring nurse coaching and peer support

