**Table 1 Tab1:** Description of the HWePS intervention: components, theoretical rationale, aims, and implementation information

Component	Theoretical Rationale	Detailed Intervention Description	Specific Aim	Intervention Level
1. Health literacy intervention based on both community and individual needs assessments	- ECCM: Decision support - Comprehensive HL intervention model	- Community-wide, multi-channel health information delivery service (SMS or postal mail) based on a community health survey and other relevant reports/documents related to community health needs - Individualized needs assessment using interRAI CUSR producing health and functional profiles and risk triggers based on evidence-based algorithms	- Promote health literacy for older people, community lay health leaders (CLHLs), and the care team - Increase health awareness - Facilitate communication between the community and the public health center (the intervention team)	-Individual -CLHLs (peers) & health professionals - Community
2. Personalized (self-)care management with a nurse-led multidisciplinary team and peer support by community lay health leaders (CLHLs)	- ECCM: Self-management; developing personal skills; delivery system design - SPEC intervention model	- Self-care planning by older people with a nurse coach, based on the CUSR report - Features nurse coaching for self-care goal setting and skill-building education/planning, and peer support (by trained CLHLs) for keeping to the plan - Tailored intervention and information (SMS) programs for one or more triggered/preferred healthy life-style areas (diet, exercise, mood, and social relationship) by multidisciplinary care team - Community-wide walking promotion program - Nurse-led multidisciplinary care conferences (MCCs) attended by both professionals and CLHLs	- Enhance self-care of identified health problems - Improve health behaviors through self-care and coaching from care team and CLHLs - Improve health outcomes and efficacy through self-care and walking promotion - Increase easily accessible resources within the community as a window for health needs and referrals - Strengthen social support in the community	Individual

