### Outcomes

The study seeks to evaluate two primary outcomes: self-rated health and health-related quality of life (HRQoL), along with several secondary outcomes and process evaluation measures. Most primary and secondary outcomes are taken from the annual Community Health Survey, a nationwide survey conducted by the Korean CDC [38]; outcomes from other sources are indicated accordingly. All outcomes and their measurements are summarized in Table 2.

**Table 2 Tab2:** Overview of the outcome variables, measures, and observation points

Outcome	Variable	Data Source/Instrument	Measurement Points	Target Respondents
Primary	Self-rated health	WHO World Health Survey; Korea Community Health Survey	T1, T2	IG, CG
	Health-related quality of life	EuroQol (EQ)-5D-3L	T1, T2	IG, CG
Secondary	Frailty	Fried’s frailty phenotype	T1, T2	IG, CG
	Wellbeing	World Health Organization- Five Well-Being Index (WHO-5)	T1, T2	IG, CG
	Self-efficacy	Korean Self Rated Abilities for Health Practices (K-SRAHP)	T1, T2	IG, CG
	Community efficacy	Collective Efficacy Scale	T1, T2	IG, CG
	Physical activity	Korean version of the International Physical Activity Questionnaire (K-IPAQ) as presented in the Korea Community Health Survey	T1, T2	IG, CG
	Hypertension awareness, diabetes awareness, mood, stress	Single items taken from the Korea Community Health Survey	T1, T2	IG, CG
	Functional health	Scales and CAPs from interRAI Check-Up Self-Rated Version (CUSR)	T1, T2	IG
	Technology acceptance	Short version, Senior Technology Acceptance Measure (STAM)	T1, T2	IG
	Nutrition, depression	Nutrition Questionnaire Elderly (NQE), Patient Health Questionnaire-9 (PHQ-9)	T1, T2	IG participants who received tailored programs
	Satisfaction	Client Satisfaction Questionnaire	T2	IG

*IG* Intervention group, *CG* Control group

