*Functional health* is assessed from the scales and clinical action points (CAPs; e.g., falls, cardiovascular disease, pain, etc.) in the interRAI Check-Up Self-Report (CUSR) [27]. The interRAI CUSR is a multidomain geriatric assessment to screen older adults’ intrinsic capacity, designed to be administered by themselves and/or with assistance from non-health professionals in the community or primary care setting. The CUSR has good psychometric properties in other countries [27, 36] and also in Korea [34].

*Nutrition* and *depression* are measured for those who receive tailored intensive intervention programs (nutrition, emotional). For those who participate in the intensive nutrition program, the Nutrition Quotient for Elderly (NQ-E) is used to measure the nutritional status and dietary quality of older adults [51]. The NQ-E assesses nutritional status through 19 items across four domains (balance, variety, restriction, dietary behavior), which are weighted and summed to determine the respondent’s nutrition rating: low, medium–low, medium–high, or high. For those who participate in the intensive emotional program, the PHQ-9 is used to measure depression. The PHQ-9 comes from the Patient Health Questionnaire developed by Kroenke et al. [52] and translated into Korean by Han et al. [53]. The Korean version of the PHQ-9 has good internal consistency (0.88) and convergent validity (0.74).

*Program satisfaction* is collected using a modified version of the Client Satisfaction Questionnaire, with 8-items that evaluate the participants’ program satisfaction. The measure, which has been translated by Hwang [54], is widely used for Korean public programs.

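### Uncontrolled paired t-tests on intervention-only outcomes cannot show programme effect, and for PHQ-9 and NQ-E regression to the mean can by itself give a significant result

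*Protocol article*

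**What the plan says.** The Data analysis plan, under Effect evaluation, defines the primary analysis as intervention area against control area. For the remaining variables it states that "two paired t-tests will be applied for those variables collected only in the intervention group", and that "p-values with α ≤ 0.05 will be considered significant". The test, the threshold and the heading are therefore fixed in the protocol itself.

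Table 2 (Outcomes) shows which variables this covers. Four secondary outcomes are collected at T1 and T2 in the intervention group only: CUSR functional health (scales and clinical action points, CAPs), technology acceptance, NQ-E and PHQ-9. The last two are restricted further, to "IG participants who received tailored programs". The text under Secondary outcome measures agrees: "For those who participate in the intensive emotional program, the PHQ-9 is used to measure depression", with a parallel statement for the nutrition programme and the NQ-E.

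Table 1 (Components of the HWePS) describes entry to these programmes: "Tailored intervention and information (SMS) programs for one or more triggered/preferred healthy life-style areas". The triggers come from the CUSR, which lists risks "using triggers derived from evidence-based algorithms". A participant can therefore enter by a CUSR trigger or by preference.

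**The concern.** A before–after test in one arm attributes every change over about 13 weeks to the programme. Time trend, pandemic change (the Discussion itself names the pandemic as an external threat to the results) and retesting effects are all included. This applies to all four outcomes.

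PHQ-9 and NQ-E carry a second problem. Some people are measured because a check-up flagged a need. Where the flag partly reflects a temporarily poor state, the follow-up value drifts back towards the person's usual level with no treatment effect, and the paired test counts that drift as improvement.

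There is also a mismatch of test and scale. CAPs are triggered or not triggered, and the NQ-E ends in a four-level rating. A paired t-test suits neither.

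The results fall under an effect-evaluation heading, and the protocol foresees spreading the model in whole or by component if it works. An uncontrolled p-value on the nutrition or emotional programme could be read as evidence for that component.

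**Working it through.** **1. Which threat applies to which outcome** (Table 2, Secondary outcome measures)

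| Outcome | Measured in | Control value | Selected on trigger or preference |
|---|---|---|---|
| CUSR scales and CAPs | whole intervention group | none | no |
| Technology acceptance | whole intervention group | none | no |
| NQ-E | nutrition-programme entrants | none | yes |
| PHQ-9 | emotional-programme entrants | none | yes |

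Satisfaction is also intervention-only but is measured at T2 alone, so no paired test is possible for it.

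**2. Plan's own figure.** The protocol gives no sample size, SD, retest correlation or power for these tests, so there is nothing to reproduce. All inputs below are assumptions except the 5% level, which is taken as two-sided.

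**3. Model with zero true effect.** Baseline X1 and follow-up X2 are standardised, with retest correlation ρ = 0.7. The worst share q = 0.3 on a screening score S is selected, and S has correlation r with X1. If S shares the transient part of X1, the expected spurious improvement is

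shift = r · (1 − ρ) · φ(c)/q

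With q = 0.3, c = 0.524 and φ(c) = 0.348, so φ(c)/q = 1.159 and (1 − 0.7) × 1.159 = 0.348.

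- r = 1 (selection on the outcome itself): 0.35 SD
- r = 0.6: 0.6 × 0.348 = 0.21 SD
- r = 0.4: 0.4 × 0.348 = 0.14 SD
- Half triggered at r = 0.6, half drawn from untriggered people: 0.5 × 0.209 − 0.5 × (0.6 × 0.3 × 0.348/0.7) = 0.104 − 0.045 = 0.06 SD
- S related only to the stable part of the outcome: 0

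**4. Chance of a significant improvement.** Two-sided 5% paired t-test, counting improvements only (nominal 2.5%), 4,000 simulated trials per setting:

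| Entry route | Shift (SD) | n = 30 | n = 50 | n = 100 |
|---|---|---|---|---|
| Trigger shares only the stable part | 0 | – | about 2.3% | about 2.3% |
| Half triggered (r = 0.6), half not | 0.06 | – | 7% | 12% |
| Trigger, r = 0.4 | 0.14 | 16% | 25% | 45% |
| Trigger, r = 0.6 | 0.21 | 32% | 47% | 76% |
| Selection on the outcome itself | 0.35 | – | 91% | 99.7% |

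Hand check for r = 0.6, n = 50: k = 1.159 × (1.159 − 0.524) = 0.736. Variance of change = (1 − ρ)²(1 − r²k) + (1 − ρ²) = 0.09 × 0.735 + 0.51 = 0.576, so SD = 0.759. Expected t = 0.209 × √50 / 0.759 ≈ 1.94 against a critical value of 2.01, and Φ(1.94 − 2.01) ≈ 0.47. This agrees with the table.

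**The case against.** A reader might infer that regression to the mean makes a significant improvement close to certain. The arithmetic for that exists: selecting the worst 20% on the outcome itself at ρ = 0.7 gives 0.3 × 0.280/0.2 = 0.42 SD, and a paired test with n = 50 is then significant in about 99% of simulated trials. The documents do not describe that selection. The trigger is the CUSR, a different instrument; nothing says that PHQ-9 or NQ-E selects anyone; and entry is partly by preference. The number of entrants and the correlations are not given. Nor do the documents say whether the T1 PHQ-9 or NQ-E precedes or follows the trigger; if it follows, some of the regression has happened before baseline. This objection stands and limits the point to what can happen.

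A reader might also extend regression to the mean to every intervention-only outcome. CUSR measures and technology acceptance are taken in the whole intervention group, so trigger selection does not apply to them. They remain uncontrolled. The roll-out in three clusters over about 12 months softens the seasonal part of that objection but does not supply a comparator.

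On test choice, the NQ-E items are weighted and summed before rating, so a score exists, and the CUSR includes scales as well as CAPs. The mismatch is therefore firm for CAPs, and conditional for the NQ-E on the four-level rating being what is analysed.

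Finally, no passage says that a significant paired test will be claimed as effectiveness. That is true, but the tests are placed under effect evaluation with a significance threshold, and no caveat is attached.

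**Conclusion.** The point holds in limited form. The protocol fixes uncontrolled paired t-tests as part of effect evaluation for four secondary outcomes, and nothing elsewhere repairs this. For all four, programme effect is confounded with time, pandemic and retest change. For PHQ-9 and NQ-E, regression to the mean is an added source of apparent improvement.

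Its size cannot be fixed from the documents. Under the stated assumptions at n = 50, the chance of a false significant improvement runs from nominal to about 91%. The top of that range requires selection on the outcome itself, which the protocol does not describe. The intermediate settings give 7% to 47%, about 3 to 19 times the nominal 2.5% (7/2.5 and 47/2.5). The comparison of areas on the two primary outcomes does not depend on any of this.

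**What to change.** Under Effect evaluation, replace the paired-t-test sentence with a rule of this kind:

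- Outcomes collected only in the intervention group are reported descriptively as change with 95% CI, labelled uncontrolled, with no claim of effectiveness.
- PHQ-9 and NQ-E results carry an explicit regression-to-the-mean caveat.
- CAPs and NQ-E categories are shown as T1-to-T2 transition tables. If any test is run, it is McNemar for binary items or a paired ordinal test for the rating.
- Effect claims rest on outcomes that both arms complete, such as WHO-5, the mood and stress items and frailty. These are not presented as substitutes for CUSR functional health or for nutrition, which have no controlled counterpart in this design.

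The cost is wording, and some secondary results become descriptive. No new data are needed. The Trial status section says that analysis has not started, so on that footing the change can still be prespecified.

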#### Process analysis

Quantitative data will be analyzed using simple descriptive analyses using SAS 9.4 (Cary, NC, USA), including the logs from the HWePS ICT system, the HWePS app, and the Walk-On app (a community walking tracking app) in order to monitor delivery of the intervention. We will also analyze the standardized-questionnaire item responses from participants and lay-leaders, participants’ attendance documents, participants’ self-practice records, etc.

In addition, qualitative data will be analyzed using thematic analysis in MAXQDA qualitative software. These data include the semi-structured questionnaire responses from lay-leaders/multidisciplinary teams, focus group interviews with multidisciplinary teams/lay-leaders/participants, case studies from multidisciplinary team meetings, lay-leader documents, meeting/event reports, etc.

### Ethics and dissemination

This study was approved by the institutional review board (IRB) of human subjects at Seoul National University (SNU IRB 2011/002–016). No critical modifications have been made to the protocol thus far and any changes in the future will be reported to the relevant parties. All data including personal information is saved on a password-protected computer within a locked laboratory, and only the PI and those with permission from the PI will receive access to the final dataset. None of the investigators have financial or competing interests.

The HWePS model is being tested within the context of designing a community care model in preparation for a super-aged society. From the initiation of the study, the contents of the intervention have been designed with community-level dissemination of the model in mind. input from various stakeholders has been sought in the design and implementation process of the intervention. Jungnang-gu and Seoul are planning administrative and educational activities to disseminate the HWePS model, either in part or in whole, into other areas in the district (*gu*) and the city, along with the various protocols/materials/resources developed, if the intervention is effective. Scientific dissemination of the trial results will include presentations at academic conferences, publishing in peer-reviewed journals, and reporting to a trail registry. The results will be reported regardless of effect size or direction. Authorship eligibility will follow the ICMJE guidelines, and we have no plan to hire professional writers.

### Trial status

The study has been rolled out to the intervention and control communities, and data collection is ongoing at the submission of this manuscript. Data analysis has not yet started.

## Discussion

While healthy aging for all is widely accepted public health agenda, few multi-faceted, multi-level health equity interventions promoting health and wellness exist, especially ones targeting relatively healthy older adults residing in an urban, low-income community in a non-Western country. In Korea, public health centers typically offer provider-driven, individual-level, health behavior monitoring or modification programs for people who are willing to participate [60]. Current visiting health services mainly target low-income people and prioritize those with pre-existing serious health conditions requiring immediate, intense attention with limited resources [61]. It is also challenging to organize community-wide activities to address middle- and/or upper-stream social determinants of health in order to reduce inequality in current public health practices [62].

We designed the HWePS to develop and rigorously test the effectiveness of an intervention that simultaneously engages older people and neighbors (as CLHLs) and enlists community-level resources and strengths to promote the health and wellness of older people in a low-income urban community during COVID-19. If effective, the intervention, as a preventive, integrated community care model, may add great value to current efforts to reduce health disparities among urban, lower-income older populations with double (age- and income-related) risks for inequality. First, instead of a professional-driven model, the intervention is an older person-led, community-engaged, professional-support model. As a theory-driven, evidence-based public health model, the HWePS will address health inequality by empowering older adults to recognize that they are responsible for their own health, understand their own health status and risks using a decision-support tool, develop with a nurse coach their own plan for self-care skill-building, and practice it daily with peer support enhanced by ICT tools. Second, the intervention educates and empowers participating CHNs for the “visiting community service center service” program in Seoul [16], and designs and demonstrates new roles for the CHNs, whose current roles are mainly as direct care providers. In the HWePS program, these nurses act as leaders of a multidisciplinary care team, coaches for empowering older people, and mobilizers of community resources and strengths, helping to increase community capacity to build healthy living conditions in collaboration with various stakeholders in the community as well as the multidisciplinary care team. The required preparation, resources, and also challenges for the transformation of CHNs’ roles can be identified and shared with various stakeholders, including CHNs themselves and also administrators and policymakers at various levels involved in this intervention project and more broadly.

Third, peer support is a key mechanism to promote health equity for the community [63] that the HWePS adopted based on existing evidence and input from the various stakeholders in the community during the intensive intervention development process. If effective, the intervention will show that informed, motivated, trained community lay health leaders (CLHLs) can be key players in operating the intervention as close partners with of older community residents (participants) and also as catalysts who play a critical role in the community accepting and embracing the newly developed intervention program as its own. Fourth, we expect ICT tools, digital technologies including the HWePS app and SMS, to act as indispensable tools in the success of the intervention program. In particular, we are testing the effects of a tech-human hybrid model, the use of technology with human (peer) support for an older population with relatively low (e-)health literacy; this can guide a new program of research on designing more effective digital health and wellness programs to build citizen-centered, age-friendly, connected, healthy and caring communities.

There are several expected challenges. One major challenge is the ongoing COVID-19 pandemic; public health measures to stop the infection’s spread could negatively influence various parts of the intervention implementation process (e.g., participation and retention rates) [64], which in turn may impact the results of the study. The COVID-19 pandemic is an unavoidable external threat but one that, in fact, justifies the need for this health equity intervention. To overcome this challenge, rather than the in-person large-group gatherings traditional interventions use, we have developed and implemented alternative-format meetings (e.g., one-to-one meetings, small-group meetings, remote meetings, etc.) within and between older participants, peers, and professional care teams. In addition, various ICT tools have been actively adopted, including the HWePS app, SMS, phone, and virtual meeting services (e.g., Zoom); this is possible as 5G and LTE network service is readily available everywhere across Seoul, including in our intervention community.

Another challenge is that the multi-channel heath information delivery service is designed to be an essential communication channel between the community and the wellness center during COVID-19. However, the basic unidirectional communication approach with limited feedback channels may reduce the intervention effects. While the components and duration of the 12-week (self-)care management intervention are based on existing evidence from successful intervention studies, they may not be enough to motivate older adults to continue healthy lifestyles for prolonged periods. A “companion” program has been organized at the wellness center and is designed as a self-help club in the community run by older people who have completed the 12-week intervention along with support from CLHLs. It is beyond the scope of this intervention study, but the research team plans to assess the effects of the companion program. There are also limited resources, time, and political/administrative networks and support for implementing the community-wide healthy aging initiative in ways that could lead to more meaningful changes. For example, while participants have expressed income-based health-related social needs, there are limited income-earning opportunities available in the community for older people; changing upstream social/structural determinants of health inequality is hard to address in this equity intervention study. If the intervention is effective, we will help facilitate the public health center’s continuation of the HWePS program in the intervention area, promoting it as a signature program for improving the living conditions of the area, and support the program’s dissemination to other areas of Jungnang-gu and beyond; we will also encourage the Community Residence Council to enact bylaws making a new health committee under its purview.

